## Study Protocol: Tryptophan and Attention Deficit Hyperactivity Disorder

of serotonin production for the depletion to offer a significant reduction. This cannot be assumed given that the individuals may have very low levels to begin with. Based on this, the overall aim of the current study is to investigate the effects of moderating tryptophan levels on attention, motor, temporal and cognitive impulsivity in healthy and ADHD participants. To achieve this, we will assess the impact of acute tryptophan loading (low and high TRP supplementation), compared to a balanced (unmoderated tryptophan) control condition on key cognitive ADHD symptoms in:

1. Healthy control participants (HC) and unmedicated adults with a diagnosis of ADHD (ADHD-UM) to establish the effects of tryptophan on ADHD symptoms.
2. Medicated adults with ADHD (ADHD-M) in comparison to unmedicated adults with ADHD (ADHD-UM) to establish the effectiveness of tryptophan as an adjunct treatment for ADHD.

Details of supplementation: The balanced condition (BAL) contained only 40g of 100% whey powder which provided balanced amino acid availability and contained 0.566g of TRP. The low loading condition had added TRP resulting in 1.43g of TRP and the high loading condition contained 5.24g of TRP.

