## 3 OBJECTIVES AND OUTCOME MEASURES

### 3.1 Primary objectives

The purpose of the study is to assess the impact of acute tryptophan on attention and impulsivity in adults. We aim to see if tryptophan loading is effective in reducing the symptoms of ADHD in adults, both alone and in combination with ADHD medication.

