## 9 STATISTICS AND DATA ANALYSIS

### 9.1 Sample size calculation

There is no existing data to calculate considering these groups and conditions to sample size. However, similar studies covering components of the current work, indicate small-medium effects sizes, therefore a power analysis assuming this effect size and power of 0.95 was conducted. This suggests that we require a total group size of 144 participants (48 HC, 48 ADHD-M, 48 ADHD-UM).

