### 9.3 Statistical analysis plan

#### 9.3.1 Primary and secondary outcome analysis

To achieve the study's objectives, we will adopt a 3 x 3 x 2 factorial design. Factor 1, 'ADHD Status', is a between-subjects factor and consists of three distinct participant groups (healthy controls, unmedicated ADHD, medicated ADHD). Factor 2, also between-subjects, is 'Tryptophan modulation' and consists of three conditions: balanced, low loading, high loading. The final factor is within-subjects and is the 'Time' at which measures are collected i.e., before and after protein (tryptophan) consumption. Data analysis will use parametric methods, typically mixed ANOVA, after normality checks and any necessary transformations.

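### If the contrasts that answer the objectives are taken from the single mixed ANOVA, their standard errors average the change-score variance of all three groups; group-specific variances would avoid this at little cost

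*Protocol*

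**What the plan says.** Protocol section 9.3.1 ties one design to the objectives: "To achieve the study's objectives, we will adopt a 3 x 3 x 2 factorial design". The two between-subject factors are participant group (three levels) and tryptophan condition (three levels). The third factor is measurement occasion: "The final factor is within-subjects and is the 'Time' at which measures are collected". The method sentence is: "Data analysis will use parametric methods, typically mixed ANOVA, after normality checks and any necessary transformations". Normality is the only assumption check named. The section does not mention equality of variances, a model with unequal variances, or the error term for comparisons within a group.

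The questions to be answered concern particular groups. Section 3.1 asks whether tryptophan loading is "effective in reducing the symptoms of ADHD in adults, both alone and in combination with ADHD medication". The second numbered aim at the end of section 1 sets medicated against unmedicated adults with ADHD. Section 9.1 plans 144 participants, 48 in each group. No standard deviation is given for any group or outcome.

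**The concern.** An omnibus F test does not say whether tryptophan works in unmedicated ADHD, works alongside medication, or differs between the two. Follow-up contrasts must do that. In a standard mixed ANOVA the natural source of their standard error is the model's residual, which pools the three groups.

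Controls and the two ADHD groups are different populations, one of them on medication, and nothing in the protocol suggests that their before-to-after changes vary equally. If they do not, a pooled residual gives some groups too small a standard error and others too large a one. The risk is a false-positive rate above 5% in the group where a claim of benefit would be made, and a test that is too strict in another group.

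**Working it through.** **Inputs.** From the protocol: three groups of 48 (section 9.1), three conditions (sections 4 and 9.3.1), two occasions. Assumed: equal allocation to conditions, giving 48/3 = 16 per cell; two-sided 5% tests; normal change scores; no tryptophan effect. The SD ratios are assumptions, shown as a range.

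**The plan's own figure.** The total of 144 cannot be reproduced, because section 9.1 gives no numerical effect size, significance level, correlation or tested term. It is used here only for the cell size.

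**Step 1: which variance matters.** With two occasions, the tryptophan-by-time effect is a difference between conditions in mean change. Only the variance of the change counts. Stable differences between people cancel.

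**Step 2: the pooled error.** With equal group sizes the residual variance of the change estimates V = (v_HC + v_UM + v_M)/3, on 9 x 15 = 135 df. A group's own error has 3 x 15 = 45 df.

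**Step 3: within-group contrast (high versus balanced).** The true variance is 2v_g/16 and the pooled model uses 2V/16. The ratio of reported to true standard error is r = sqrt(V/v_g), and type I error is approximately 2[1 - Phi(1.96 r)].

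**Step 4: ADHD-M versus ADHD-UM.** The true variance is 2(v_UM + v_M)/16 and the pooled model uses 4V/16, so r = sqrt(V/[(v_UM + v_M)/2]). This is below 1 exactly when the mean ADHD variance exceeds the control variance.

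**Step 5: numbers** (change-score SDs in the order HC:UM:M).

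| SDs | V | r, HC / UM / M | Type I error, HC / UM / M | r, M versus UM | Type I error, M versus UM |
|---|---|---|---|---|---|
| 1:1.25:1.25 | 1.375 | 1.17 / 0.94 / 0.94 | 2.2% / 6.6% / 6.6% | 0.94 | 6.6% |
| 1:1.5:1.5 | 1.833 | 1.35 / 0.90 / 0.90 | 0.8% / 7.7% / 7.7% | 0.90 | 7.7% |
| 1:2:2 | 3.000 | 1.73 / 0.87 / 0.87 | 0.1% / 9.0% / 9.0% | 0.87 | 9.0% |
| 1:2:1.5 | 2.417 | 1.55 / 0.78 / 1.04 | 0.2% / 12.8% / 4.2% | 0.88 | 8.5% |
| 1:1.5:1.1 | 1.487 | 1.22 / 0.81 / 1.11 | 1.7% / 11.1% / 3.0% | 0.93 | 6.9% |

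Worked example for 1:2:2: V = (1 + 4 + 4)/3 = 3; r = sqrt(3/4) = 0.866; 1.96 x 0.866 = 1.70; two-sided tail area 9.0%. When the two ADHD groups are equally variable, r cannot fall below sqrt(2/3) = 0.82, which gives about 11%.

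**Step 6: simulation.** Nine cells of 16, 40,000 runs per pattern, using t and F critical values. The pooled-error rates agree with the table to within about half a percentage point (for 1:2:1.5: 12.9% in ADHD-UM and 4.5% in ADHD-M). With each group's own error, every within-group contrast lies between 4.7% and 5.3%. With an unequal-variance comparison, ADHD-M versus ADHD-UM lies between 4.9% and 5.1%. In these patterns the omnibus tryptophan-by-time test is at about 5%, and group-by-tryptophan-by-time is between 5.0% and 5.9%.

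**The case against.** The strongest reply is that the protocol does not say how effects within a group will be tested. The word typically leaves room for separate analyses by group, and error terms for follow-up contrasts are commonly left to a statistical analysis plan, which may exist. That stands, and it makes the point conditional on the contrasts being taken from the model that section 9.3.1 names. The point still applies to stated text, because that section chooses the model, says it serves the objectives, and names the one assumption to be checked.

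Second, no SDs are given, so larger variance in ADHD is an assumption. Greater spread in level alone does no harm, and the transformations mentioned may also even out variances. All of this stands. The transformations are, however, linked to normality checks, and nothing in the section targets equal variances.

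A reader might go further in three ways that are not supported:

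- **That ADHD standard errors are too small whenever ADHD participants vary more than controls.** With SDs 1:2:1.5, ADHD-M varies 1.5 times as much as controls, yet its variance of 2.25 lies below the average of 2.417 and its standard error is too large.
- **That a real effect in controls would be almost undetectable.** By normal approximation, a control effect with 80% power under its own variance keeps about 69%, 56% and 28% at SD ratios of 1.25, 1.5 and 2. That is a real loss, but not the stronger claim.
- **That the main ANOVA is invalid.** With equal cells its omnibus tests, including the interaction that compares groups directly, stay close to 5%.

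**Conclusion.** The point holds in conditional form. If the tryptophan contrasts within ADHD-UM, within ADHD-M and between the two are taken from the single mixed ANOVA, their error variance is the three-group average. The within-group test is then too liberal for any group whose change-score variance exceeds that average and too strict for any group below it. The ADHD-M versus ADHD-UM contrast is too liberal when the mean ADHD variance exceeds that of controls.

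The size depends on SDs that the protocol does not give. With equal ADHD SDs of 1.25 to 2 times the control SD, standard errors in the ADHD groups are about 6% to 13% too small, and type I error is about 6.5% to 9%. Unequal ADHD groups can push one of them to about 13% while the other falls below 5%. These figures assume 16 per cell and normal change scores. Neither the unequal variances nor the use of a pooled follow-up error is established by the document, so this is a worthwhile improvement rather than a proven fault.

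**What to change.** Add one sentence to Protocol section 9.3.1: tryptophan contrasts within each participant group, and the comparison of ADHD-M with ADHD-UM, will use group-specific variances. This can be done in either of two ways:

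- use each group's own error for the within-group contrasts and an unequal-variance comparison between groups; or
- fit a linear mixed model whose residual variance and pre-post covariance are estimated separately for HC, ADHD-UM and ADHD-M, with Satterthwaite or Kenward-Roger degrees of freedom.

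The omnibus tests can stay as planned. If variances are in fact equal, the within-group error df fall from 135 to 45, and the critical t rises from 1.98 to 2.01 (2.014/1.978 = 1.018), so intervals widen by under 2%. No additional participants or data are needed.

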## 10 PARTICIPANT POPULATION

Adults aged 18-35 years with or without a diagnosis of ADHD.

## 11. DATA MANAGEMENT

### 11.1 Data collection tools and source document identification

Participant data is collected in the online screening survey via the platform, Qualtrics. This data contains an email address which is only accessible to the research completing screening and allocation and is held securely on university, password-restricted storage. Participant files are produced during each testing session within the online experiment platform (Gorilla). These do not contain identifiable information but rather a participant ID. Documents linking IDs to participants screening data are securely held within a restricted-access OneDrive for Business account which is password-protected and accessible only to the immediate research team (and only to the researcher completing allocation until after all data collection is completed).

### 11.2 Data handling and record keeping

Participants' anonymised personal data is securely stored on a restricted-access OneDrive for Business folder to which only the immediate research team has access. These files are also stored on password-protected university, personal and laptop computers as necessary for analysis. However, the master spreadsheet which contains the participants' e-mail addresses correlated with their unique IDs is password-protected and only the researcher conducting allocation has access to this.

### 11.3 Access to Data

Direct access will be granted to authorised representatives from the Sponsor, host institution and the regulatory authorities to permit trial-related monitoring, audits, and inspections- in line with participant consent.

### 11.4 Archiving

Fully anonymised data will be made available on the institutional repository once the work is published.

## 12 ETHICAL AND REGULATORY CONSIDERATIONS

### 12.1 Research Ethics Committee (REC) review& reports

The study has received ethical clearance from the Psychiatry Nursing and Midwifery Research Ethics Subcommittees (PNM RESC) under the reference number HR-19/20-17983.

### 12.2 Peer review

No external funding was required for this research and as such no funder peer review occurred. The quality of the research was assessed within the research team, between the Principal Investigator and the co-investigators (at King's College and Sheffield University).

### 12.3 Public and Patient Involvement

We plan to work with people with lived experiences in undertaking the research and dissemination of findings through existing links to various groups including the Young People's Mental Health Advisory Group. The members of the group are aged 16-26, which overlaps very well with our target sample (18-35). We are hoping that we can discuss our project in more detail and feedback their advice into how we are conducting the study, how can we make the project more enjoyable for individuals with lived experiences of ADHD and what possibilities of dissemination are optimal for reaching a larger, more diverse audience.

### 12.4 Data protection and patient confidentiality

Data will be processed in accordance with the General Data Protection Regulation (GDPR, 2018) and the Data Protection Act (2018).

On receipt of screening survey data, email addresses will be removed from the dataset and replaced with a participant ID, meaning screening data will be stored anonymously. This ID will then be used for all data collected. Email addresses will be stored separately to allow participants to be contacted for booking in testing times. During the study all data will be stored on secure university servers, accessible to only the research team.

At the end of the study, email addresses will be deleted, and fully anonymised data will be stored on the university servers for up to five years after publication of the work, accessible only to the researchers. Should a suitable online data repository be available, a full set of anonymised data will be placed on the platform to allow future accessibility (likely institutional repository).

Participants will not be identifiable from any outputs of the project (e.g. report).

The only individuals who will have access to the personal data of the participants are those involved in allocation of the participants to conditions and booking them in.

The data generated by the study will be analysed by the Research Assistant, Principal Investigators and undergraduate and postgraduate students. All datasets will be fully anonymised. All data will be fully

### 12.5 Financial and other competing interests

There is no conflict of interest.

### 12.6 Indemnity

The sponsor, King's College London, will take primary responsibility for ensuring that the design of the study meets appropriate standards and that arrangements are in place to ensure appropriate management, design, conduct and reporting. King's College London provides cover under its No Fault Compensation Insurance, which provides for payment of damages or compensation in respect of any claim made by a research subject for bodily injury arising out of participation in human volunteer studies (with certain restrictions).

### 12.7 Access to the final study dataset

The final trial dataset will be fully anonymised. The Principal Investigator will have access to the final dataset. A copy of the anonymised dataset might be published on an online data repository if a suitable one becomes available.

## 13 DISSEMINATION POLICY

### 13.1 Dissemination policy

The results will be disseminated through internal reports, peer-reviewed journals and at national and international conferences. This research study will lead to the generation of intellectual property, which will be the property of the Principal Investigator.

### 13.2 Authorship eligibility guidelines and any intended use of professional writers

Authorship will be granted to members of the research group who have made an important contribution to the conduct, analysis and dissemination of the study's findings.

